## Abstract

**Background:**

N-of-1 trials promise to help individuals make more informed decisions about treatment selection through structured experiments that compare treatment effectiveness by alternating treatments and measuring their impacts in a single individual. We created a digital platform that automates the design, administration, and analysis of N-of-1 trials. Our first N-of-1 trial, the app-based Brain Boost Study, invited individuals to compare the impacts of two commonly consumed substances (caffeine and L-theanine) on their cognitive performance.

**Objective:**

The purpose of this study is to evaluate critical factors that may impact the completion of N-of-1 trials to inform the design of future app-based N-of-1 trials. We will measure study completion rates for participants that begin the Brain Boost Study and assess their associations with study duration (5, 15, or 27 days) and notification level (light or moderate).

**Methods:**

Participants will be randomized into three study durations and two notification levels. To sufficiently power the study, a minimum of 640 individuals must begin the study, and 97 individuals must complete the study. We will use a multiple logistic regression model to discern whether the study length and notification level are associated with the rate of study completion. For each group, we will also compare participant adherence and the proportion of trials that yield statistically meaningful results.

**Results:**

We completed the beta testing of the N1 app on a convenience sample of users. The Brain Boost Study on the N1 app opened enrollment to the public in October 2019. More than 30 participants enrolled in the first month.

**Conclusions:**

To our knowledge, this will be the first study to rigorously evaluate critical factors associated with study completion in the context of app-based N-of-1 trials.

**Trial Registration:**

ClinicalTrials.gov NCT04056650; https://clinicaltrials.gov/ct2/show/NCT04056650

**International Registered Report Identifier (IRRID):**

PRR1-10.2196/16362

## Introduction

### Background

The purpose of this study is to evaluate factors that may impact study completion and adherence in the context of app-based N-of-1 trials. A common challenge for digital research studies is the poor engagement of users [1]. The “law of attrition,” as Eysenbach described it in 2005, is of special concern to app-based N-of-1 studies. Unlike a conventional, two-arm, randomized controlled trial (RCT) where a minimum sample size is calculated to detect a treatment effect that also takes into account an expected rate of attrition across the enrolled population, N-of-1 trials operate at the level of the individual, and there is 1 participant per trial. Typically, in an N-of-1 trial, an individual alternates between treatments (ie, “multiple crossover”), and outcomes are measured during each treatment period [2,3]. If there is attrition and the participant fails to complete an N-of-1 trial, there is no result for that individual.

Moreover, if a participant completes an N-of-1 trial, the result may still fail to achieve a level of statistical meaningfulness, especially for shorter trial durations. In this way, any person that aims to design an N-of-1 trial that is capable of informing decision-making for treatment selection for a single individual must strike the right balance between the ease of trial completion and the generation of meaningful results. Therefore, we aim to collect evidence about critical factors that may impact rates of study completion in the context of app-based N-of-1 trials. We hope these findings will inform the design of future app-based N-of-1 trials and improve the adoption of N-of-1 methods and tools.

### N-of-1 Trials

N-of-1 trials create an opportunity for individuals to optimize treatment selection more systematically. In contrast, “therapy by trial” is a more common practice in both wellness and clinical medicine and is where individuals begin a therapy and monitor outcomes, often without much formal structure. If a treatment is deemed ineffective or introduces intolerable treatment burdens, a change to the treatment is made. N-of-1 trials are an alternative approach designed to help individuals make more objective, data-driven treatment choices.

Usually, in an N-of-1 trial, an individual alternates between treatments, and outcomes are measured during each period [2,3]. Where feasible, treatments may be blinded or placebo-controlled. Outcomes are measured at baseline and each treatment period. At the end of the trial, outcome measurements for each treatment are compared, and a treatment is selected. N-of-1 trials are particularly relevant in contexts where evidence for treatment efficacy is weak or where treatment response is known to vary across patient populations [2]. N-of-1 trials may also be deployed to answer other common treatment questions, such as optimal dosage or whether a symptom is associated with a treatment’s side effects [2]. In what is considered a landmark paper for modern N-of-1 trials, Guyatt and colleagues applied this methodology to compare two treatments in a single patient with uncontrolled asthma and discovered that one treatment made the patient feel worse [4,5].

N-of-1 trials are not useful in every treatment context. Treatments with rapid onset and minimal washout are ideal candidates for N-of-1 trials, whereas curative treatments or treatments with cumulative effectiveness (eg, antidepressants) are not. N-of-1 trials are suitable for individuals with chronic or stable conditions. For example, one might compare melatonin versus herbal tea for chronic insomnia, and another might compare the effectiveness of two topical creams for persistent acne [2].

### Hypotheses

The primary hypothesis is that shorter trials will have higher rates of completion compared to longer trials. The null hypothesis is that no correlation exists between study completion and study duration. We also hypothesize that higher rates of study completion will be achieved with more frequent reminders to complete study tasks, in the form of app-based notifications, especially since the Brain Boost Study requires participants to complete tasks during a specific window of time each day during the trial. The null hypothesis is that no correlation exists between study completion and notification level.

## Methods

### Study Setting

All study activities are conducted through the N1 app, a smartphone iOS app distributed via the Apple App Store. We will primarily recruit participants via social media and through messages to online communities where there is documented interest in the topics of nootropics, supplements, medical science, or health technology. The informed consent process takes place remotely through the app, as described elsewhere [6]. Participants may contact the study staff at any time via email with questions or concerns. We have a designated health care professional on the study team to follow up on participant-reported, health-related concerns that are related to their participation in the Brain Boost Study. Participant flow through the study is described in Figure 1.

**Figure 1 figure1:**
[figure not shown]
Participant flow through the Brain Boost Study using the N1 app. E-consent: electronic consent.

### Eligibility Criteria

Adults aged 18 or older who have an iPhone running iOS 11.0 or later, consume caffeine, and live in the United States are eligible to enroll in the study. Exclusion criteria include anyone with reason to believe that consuming caffeine may be harmful to their health, are pregnant, or are breastfeeding. If a participant is unsure about whether they have a health issue that prevents them from consuming caffeine, they are advised to consult their doctor but are still eligible for the study.

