### Study Design

This study aims to evaluate a novel platform for conducting single-patient, multiple crossover studies (N-of-1 trials). For purposes of clarity, this protocol describes our methods to assess factors associated with study completion, along with several exploratory measures and analyses. The study design, interventions, cognitive assessment instruments, and methods for evaluating whether there is a detectable treatment effect for an individual participant enrolled in the Brain Boost Study based on their performance on the cognitive assessments are described elsewhere [6]. Participants enrolled in the Brain Boost Study follow a treatment schedule, guided by a mobile app (N1 app), where they alternate between the two treatments: caffeine (treatment A) or caffeine combined with L-theanine (treatment B) during a prespecified window of time. Participants are also asked to complete an app-based cognitive assessment during a prespecified window of time each day. The daily cognitive assessment includes three separate cognitive tests: the Stroop Test, the Remote Associates Test, and the Trailmaking Test [6]. They complete their tasks during one baseline period (where no treatment is assigned), and during four treatment periods where either treatment A or treatment B is assigned according to counterbalanced block design. Participants are not compensated, and the app is free to use. Only after a trial is completed does a participant see their results from the cognitive assessments.

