### Measures

#### The Proportion of Studies Completed

The primary outcome of interest is the proportion of studies completed. A study is considered complete if a participant reaches the end of a trial without a study failure (involuntary withdrawal) or voluntary withdrawal. A study failure occurs when there is insufficient data generated during baseline or any treatment period due to missed treatments (self-reported) or incomplete assessments. Participants must complete all assigned treatment and assessment tasks for 1/3 of the days in each period to avoid study failure and involuntary withdrawal, except for the 5-day study where all tasks must be completed each day because there is only one day per period. For the 15-day and 27-day trials, we inevitably expect participants to miss some tasks during these periods, so we wanted to allow for some nonadherence. While the requirement of task completion for 1/3 of the days in each treatment period is somewhat arbitrary, the choice of 1/3 of the days means that, at a minimum, completed 15-day trials will at least have the same amount of data as completed 5-day trials and are also likely to have more. We applied the same criteria to the 27-day trial so that the criteria for study failure are uniform across all three study durations. It is also worth noting that the 3 study lengths are primarily dictated by our randomized, counterbalanced, crossover design that defines N-of-1 trials: NABBA or NBAAB, where N is baseline, A is treatment period A, B is treatment period B, and AB or BA is a block. The minimum N-of-1 trial for a counterbalanced design with two blocks is five days if you have only one day per treatment period and one day of baseline.

We anticipate that a 27-day trial approaches what is likely to be the maximum number of days we could expect people to participate with reasonable adherence for this study, which requires daily tasks. The 15-day trial splits the difference between these two extremes. Put another way, we chose to vary treatment period lengths by one day for the 5-day trial, three days for the 15-day trial, and five days for the 27-day trial. We could have selected a different design, such as treatment periods that are 1, 2 and 3 days long rather than 1, 3 and 5 days long for each group; however, to evaluate the impact of study durations and notification levels on completion rates, we reasoned it would be better to have a more extensive spread across the three groups.

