## Discussion

### Primary Findings

The N1 App aims to facilitate the design, administration, and analysis of N-of-1 trials. The Brain Boost Study will be the first experiment available on the platform that is open to the public. As a wellness-related study that evaluates the effect of commonly used supplements on cognitive performance, this study also provides an opportunity to socialize N-of-1 methods to much broader audiences. While the first intentionally designed crossover treatment trial dates to the late 1700s and N-of-1 trials like how we conceive of them today have been practiced for decades, adoption remains low [10-12]. Opportunities for the public to apply these methods to their treatment dilemmas are similarly scarce outside of a limited number of clinical settings with expertise in the design, administration, and analysis of N-of-1 trials.

Digital tools, like the N1 app, provide a promising new avenue for making N-of-1 trials more accessible. However, many challenges remain, especially around participant engagement and adherence in app-based research [13]. Sustained engagement of participants has been elusive for many digital health studies to date. In a pooled analysis of 8 app-based digital health studies representing over 100,000 participants, 850,000 study days, and 3.5 million app-based tasks, the median time participants engaged in the study during the first 12 weeks was only 5.5 days, and the median time participants performed active tasks was only two days [14]. To deploy an effective app-based N-of-1 trial, one must reconcile many trade-offs that span study design, technology, and user characteristics. To our knowledge, this will be the first study to rigorously evaluate multiple factors associated with study completion and adherence in the context of app-based N-of-1 trials. One other app-based N-of-1 trial platform has recently evaluated usability and user acceptance of an app in the context of pain-related N-of-1 trials [15,16]. Our findings should be of significant interest to practitioners seeking to design N-of-1 trials using similar methods and tools to support data-driven treatment choices.

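### The harm exclusion and the doctor-consultation advice cover caffeine only, although every participant is also assigned L-theanine

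*Protocol article*

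**What the plan says.** Two sentences in Eligibility Criteria deal with harm from a study substance.

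- The exclusion: "Exclusion criteria include anyone with reason to believe that consuming caffeine may be harmful to their health, are pregnant, or are breastfeeding".
- The advice to anyone who is "unsure about whether they have a health issue that prevents them from consuming caffeine, they are advised to consult their doctor". That person remains eligible.

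The inclusion rule requires participants to be caffeine consumers. It says nothing about L-theanine.

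Under Study Design, participants follow a schedule in which "they alternate between the two treatments: caffeine (treatment A) or caffeine combined with L-theanine (treatment B"). The section The Proportion of Studies Completed gives the only two sequences: "NABBA or NBAAB, where N is baseline, A is treatment period A, B is treatment period B".

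In the Discussion (Strengths and Limitations) the authors describe their entry rules as broad and as directed at caffeine safety.

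**The concern.** The trial assigns two substances, but the self-declared harm screen is written for one of them. It is also the one that participants must already be using. For L-theanine the article states no prior-use condition, no harm exclusion and no prompt to see a doctor.

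All study activities run remotely through the app, and Eligibility Criteria describes no clinician check at entry. The participant's own declaration is thus the stated harm screen, and its wording decides whom it reaches. What is at stake is participant safety at entry. The trial's inference is not at stake.

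**Working it through.** The plan gives no figure to reproduce here, so the check is a comparison of the text with a count.

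**1. Scope of the harm sentences (Eligibility Criteria).** There are two. Both name caffeine (2 of 2) and neither names L-theanine (0 of 2). The pregnancy and breastfeeding exclusions apply whatever the substance, but they do not reach someone with another reason to avoid L-theanine. No other section of the article adds a criterion about L-theanine.

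**2. Who is assigned L-theanine (Study Design; The Proportion of Studies Completed).**

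| Sequence | Treatment periods | Periods with B |
|---|---|---|
| NABBA | A, B, B, A | 2nd and 3rd: 2 of 4 |
| NBAAB | B, A, A, B | 1st and 4th: 2 of 4 |

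No sequence omits B. Treatment periods last 1, 3 and 5 days in the 5-, 15- and 27-day trials, so the scheduled L-theanine days per person are 2 × 1 = 2, 2 × 3 = 6 and 2 × 5 = 10. This shows that assignment to L-theanine is universal. It does not measure how many people the gap affects.

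**3. Is eligibility left to another document?** Study Design lists what is described elsewhere: "The study design, interventions, cognitive assessment instruments, and methods for evaluating whether there is a detectable treatment effect for an individual participant". Study Setting adds consent: "The informed consent process takes place remotely through the app, as described elsewhere [6". Eligibility is in neither list. The article states the rule itself, and the Discussion confirms that it is about caffeine.

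**4. Possible size (assumption only).** The document does not say how many caffeine users have a known reason to avoid L-theanine. Taking 0.1% to 1% of the 640 who must begin (Power and Sample Size):

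- 0.001 × 640 = 0.64, about 1 person
- 0.01 × 640 = 6.4, about 6 people

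If they were excluded and 640 kept:

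- 640 / 0.999 = 640.6, so 641 people (1 more)
- 640 / 0.99 = 646.5, so 647 people (7 more)

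**5. How much of the sample a correction could still reach.** The only enrolment count given is more than 30 in the first month (Abstract, Results). Reading that as 31 to 39, again an assumption, gives 31/640 = 4.8% to 39/640 = 6.1%. The comparison is approximate, because the count is of people enrolled while 640 is the number who must begin.

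**The case against.** The strongest reply is that nothing here is wrong or contradictory. Eligibility Criteria and the Discussion agree with each other, and broad, caffeine-focused entry rules are how the authors describe their own design. No L-theanine hazard is documented. The Discussion presents the trial in these terms: "As a wellness-related study that evaluates the effect of commonly used supplements on cognitive performance". Caffeine is taken in all four treatment periods and L-theanine in two, so identical treatment of the two is not self-evidently required. Someone who knows of a reason to avoid L-theanine is unlikely to volunteer for an unpaid study that names it, and can decline, withdraw or contact staff. The article says: "We have a designated health care professional on the study team to follow up on participant-reported, health-related concerns". The exclusion list may not be exhaustive, and the consent text, which is not shown, may already mention L-theanine. Finally, nothing in the document anchors the 0.1% to 1% range.

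Much of this stands, and it limits the weight of the point. There is no documented hazard, the number affected is probably very small, the range is illustrative only, and unseen app text may already cover the matter.

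It does not close the gap. Consent, withdrawal and follow-up of reported concerns are not eligibility rules applied before assignment. A non-exhaustive reading of the exclusions sits poorly with the Discussion's own account of them. The authors also judged a self-declared screen and a prompt to see a doctor worthwhile for a substance that participants already consume. The article gives no reason for not extending them to one that participants need not have used before.

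**Conclusion.** The point holds, as a minor one. As written, a caffeine user who knows of a reason to avoid L-theanine meets the entry criteria and will be assigned it in two of four treatment periods. This follows directly from the text and needs no assumption.

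Its size cannot be established from the document. About 1 to 6 people per 640 is what an assumed share of 0.1% to 1% would give. Confidence that the gap matters in practice is moderate at most, because the app's screening and consent text is not shown and no specific hazard is identified. The comparisons of study duration and notification level, the power and the primary analysis do not change.

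**What to change.** In Eligibility Criteria, replace *caffeine* with *caffeine or L-theanine* in the harm exclusion and in the doctor-consultation sentence. Align the remark in Strengths and Limitations so that it refers to the safety of both substances. Check the app's screening and consent text and, if it does not already cover L-theanine, make the same change there for people not yet randomised. Keep caffeine use as the inclusion criterion and do not require prior L-theanine use.

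The cost is one phrase in each of three sentences, plus a small IRB amendment if the app text has to change. Under the assumed range, holding the number who begin at 640 would take 1 to 7 more people. At the first-month count most of the planned sample was still to be enrolled, so a change made then would have covered nearly all of it. Design, power and analysis stay as they are.

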### Study Design

This study aims to evaluate a novel platform for conducting single-patient, multiple crossover studies (N-of-1 trials). For purposes of clarity, this protocol describes our methods to assess factors associated with study completion, along with several exploratory measures and analyses. The study design, interventions, cognitive assessment instruments, and methods for evaluating whether there is a detectable treatment effect for an individual participant enrolled in the Brain Boost Study based on their performance on the cognitive assessments are described elsewhere [6]. Participants enrolled in the Brain Boost Study follow a treatment schedule, guided by a mobile app (N1 app), where they alternate between the two treatments: caffeine (treatment A) or caffeine combined with L-theanine (treatment B) during a prespecified window of time. Participants are also asked to complete an app-based cognitive assessment during a prespecified window of time each day. The daily cognitive assessment includes three separate cognitive tests: the Stroop Test, the Remote Associates Test, and the Trailmaking Test [6]. They complete their tasks during one baseline period (where no treatment is assigned), and during four treatment periods where either treatment A or treatment B is assigned according to counterbalanced block design. Participants are not compensated, and the app is free to use. Only after a trial is completed does a participant see their results from the cognitive assessments.

### Randomization

The study duration is either 5, 15, or 27 days. Participants will be randomized into study duration according to the allocation of 20%, 60%, and 20%, respectively. The uneven allocation to study duration was chosen out of consideration for the trade-offs between various study lengths. While we hypothesize that 5-day study lengths are more likely to be completed, they are also less likely to generate a meaningful result due to the small number of outcome measures. On the other hand, 27-day studies are more likely to generate a meaningful result with more repeated outcome measures, but we hypothesize that they are more likely to result in early withdrawal. Allocating more people to the 15-day study is a reasonable compromise between these two extremes, which is reflected by our decision to allocate more participants into this group while maintaining a sufficient sample size for each group to assess our primary outcome measure, as described below.

Notification level is defined as the frequency participants receive reminders to complete study tasks and is either light or moderate. Participants are randomized into the notification level, such that 50% of participants are in each group. Participants randomized into the light notification group receive two notifications per day: one reminder to take their treatment and one reminder to complete the assessment (see Multimedia Appendix 1). Participants randomized into the moderate notification level receive 4-5 notifications per day: 2 reminders to take their treatments and 2-3 reminders to complete their assessment (see Table 1).

**Table 1 table1:** Notification levels for the Brain Boost Study.

Notification level	Treatment reminders	Assessment reminders
Light	At treatment time	At assessment time
Moderate	15 minutes before At treatment time	15 minutes before At assessment time 15 minutes before the end of assessment window, only if the assessment is incomplete at this time

